#### Adjustment and interpretation based on contamination checks

If contamination is detected, we will take the following steps to adjust or interpret the study results:

Quantification of Contamination: We will quantify the extent of contamination by calculating the percentage of participants who have been exposed to details about interventions other than their own.Statistical Adjustment: We will use statistical techniques to adjust for contamination. For instance, we might include contamination status as a covariate in our regression models to control for its potential impact on the study outcomes.Sensitivity Analyses: We will conduct sensitivity analyses to assess the robustness of our findings. This will involve comparing the results of the main analysis with those obtained after excluding contaminated participants or adjusting for contamination.Interpretation of Results: In the discussion section, we will interpret our findings in light of the contamination checks. We will acknowledge the presence of contamination, describe its potential impact on the study outcomes, and discuss how our adjustments have accounted for it.

This SAP will be reviewed and updated as necessary throughout the study to ensure the robustness and integrity of the analyses and findings.

### Risk mitigation strategy

As PEH are a vulnerable group, several risk mitigation strategies have been put in place to ensure the safety and wellbeing of the participants. These are as follows:

Informed Consent will be obtained from each participant, after providing them with oral and written information clearly explaining the purpose, procedures, potential risks, and benefits of the intervention. To ensure that the participants understand their rights, the voluntary nature of participation, and their ability to withdraw at any time without consequences, they will be asked to repeat the information in their own words, orally and in writing, to the research team.To facilitate compliance with the intervention, the project staff will be drawn from the volunteers who are involved in the day-to-day activities of our organization, engaging regularly with our PEH clients. The trained teachers who will administer the interventions will be from external organizations; this will help the participants engage with organizations other than our own, thus deepening their engagement with civil society. To maintain objectivity and minimise the possibility that the participants may feel coerced to participate in the research on account of being approached by volunteers they frequently engage with, the research team is kept separate from the client engagement teams in our organization.Secure online platforms will be used in adherence to data protection regulations of our organization to safeguard personal data of all stakeholders. The smartphones used for sending and receiving correspondence and photographs of the filled K10 questionnaires will be those provided by the organization. The project staff will not use their personal phone numbers for communication with the participants under any circumstance.Keeping the culture of India in mind, the participants will be asked to provide oral consent from their next of kin. This will be recorded on the consent forms and countersigned by the participant. In case the participant is unable to read or sign their name, the consent process will be conducted in the presence of two healthcare professionals who are not related to our organization. A blank informed consent form in English and Hindi has been provided as S1 File. The informed consent forms in other languages (Tamil, Telugu, and Bengali) are true translations of the informed consent form in English.The participants’ technological access and proficiency will be assessed at the time of obtaining consent to ensure that they can fully engage with the online intervention. In case technological proficiency needs to be improved, digital literacy training and training on the digital platforms to be used in the intervention will be provided.

### Plan for dissemination of results

Upon completion of the trial, a comprehensive plan for dissemination and publication of the results will be implemented. This includes presenting the findings at relevant conferences, submitting manuscripts to peer-reviewed journals, and sharing the outcomes with key stakeholders, policymakers, and other community organizations working with PEH. Authorship will be given to members of the research team who also contribute to writing of the manuscripts; all others will be acknowledged. The final dataset will be published in a public repository upon publication of the results of the study. Additionally, efforts will be made to communicate the findings in accessible formats, such as infographics or plain language summaries, to reach a broader audience and promote the potential impact of the intervention. Specifically tailored to PEH, community meetings and community engagement volunteers will be utilized to directly engage the PEH and share the trial results in relatable and accessible formats including videos and memes. Peer educators will be trained to disseminate information and digital platforms such as WhatsApp will be leveraged to provide informational materials, empowering PEH to make informed decisions about their wellbeing.

### Timeline

Engagement with PEHs begins in Week 1, followed by a 4-week recruitment period. Baseline measurements will be conducted in Week 5, interventions in Weeks 6–7, and post-intervention assessments in Weeks 8, 12, and 56. Interim analysis shall be conducted in Weeks 13–19, and results will be published as the Stage II of this registered report. Final analysis will be conducted in Weeks 57–61, and results shall be published as a brief report. Conferences, meetings, workshops, and other community engagement events to disseminate the results of the study will be ongoing indefinitely, starting from the date of publication of the interim analysis as a registered report. The detailed timeline is shown in Fig 3.

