**Methods and analysis:**

Participants will be allocated into Bhagavad Gita, Kuchipudi dance, Both interventions, or Control groups. The Kessler scale (K10) score, representing the primary outcome, will be measured at four time points: one day before intervention, one day after intervention completion, 40 days post-intervention, and 1 year post-intervention. The K10 scores will be analyzed using the Generalized Estimating Equation framework. Additionally, subgroup analysis based on participant demographics (e.g., age, education, religion, employment) will be conducted to explore potential differential effects using analysis of covariance. Statistical significance will be determined at p < 0.05 (two-tailed).

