### Participants

Persons meeting the criteria for the definition of a houseless person—someone who does not live in a building or "census houses," but rather in the open or seeks shelter in public places such as railway stations, under flyovers, places of worship, etc.—according to the 2011 Census of India, and residing in Chennai or Dhanbad, India during and after the Unlock 2.0 phase of the COVID-19 pandemic in India, aged >18 years will be recruited. Persons with a formal diagnosis of anxiety, depression, and any other mental illness will be excluded from the study and provided access to evidence-based treatments. All PEH availing the services of Samanjasa Foundation in Chennai and Dhanbad will be approached to participate in the study; the study information will be disseminated through the case workers. During earlier studies we found that this strategy ensures nearly 90% response rate; therefore, we are expecting a similar enrolment rate in this study as well. The participants will be divided into four groups—the Bhagavad Gita (Gita), Kuchipudi dance (Kuchipudi), both Bhagavad Gita and Kuchipudi dance (Both), and control groups—in a 1:1:1:1 ratio. The participant identification number, group assignment, four copies of a questionnaire with pre-filled participant ID and follow-up date, meeting schedule, and Zoom meeting link will be sealed in a small envelope and the envelopes will be placed in a fishbowl and shuffled. The participant ID will be generated in a random order by an independent statistician using a pseudo-random number generator script in Python 3.9.13. Group assignment will be generated in sequence by the independent statistician; the participant ID generated first will be associated with the Gita group, the second with the Kuchipudi group, the third with the Both group, the fourth with the Control group, the fifth with the Gita group, and so on. The project staff will fill and seal the envelopes with the respective contents. Once a participant provides written informed consent to participate in the study, they will be asked to pull an envelope from the fishbowl and not reveal its contents to the research team. They will also be instructed not to read the questionnaires until the sessions scheduled for the purpose of filling them out. To monitor and minimize the risk of contamination, especially given the potential for participants within the same community to communicate, the project staff will send weekly text messages to the participants regarding not sharing details about the intervention with anyone, including their family members. Additionally, the project staff will randomly contact three participants from each group via a phone call every two months and ask them if they had heard anything about the interventions in the other study groups. Furthermore, during community events and interactions, case workers will be asked to assess the level of knowledge regarding the intervention among the PEH. The participant journey is illustrated in Fig 1.

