### Interventions

The participants in the Gita group will be imparted the teachings of the second chapter of the Bhagavad Gita (all verses) for 1 week, for 60 minutes per day. The teachings of the Bhagavad Gita will be imparted by a trained teacher and the second chapter has been chosen as it is said to contain the essence of the entire Bhagavad Gita [16]. The participants in the Kuchipudi group will be taught the Kuchipudi dance choreography to a popular devotional song (“Sivashtakam”, choreographed by Padma Bhushan [name] [name], song duration is approximately 10 min) for 60 minutes per day by a trained teacher for 1 week. Every day for 1 week, the participants in the Both group will be taught the Kuchipudi dance choreography to a popular devotional song (“Vandanamu Raghunandana”, choreographed by Kala Tilakam [name], song duration is approximately 5 min), which is shorter in duration than the song used in the Kuchipudi group, for 30 minutes by a trained teacher, followed by imparting the teachings from selected verses of the second chapter of the Bhagavad Gita (Verse 40–72) for 30 minutes by a trained teacher. The participants in the control group will receive no intervention. The participants will be instructed to join their assigned groups at the scheduled meeting times using the meeting link in their sealed envelopes. Apart from the teaching sessions, meetings will also be scheduled one day before the start of the teaching sessions, one day after the end of the teaching sessions, 40 days after the end of the teaching sessions, and 1 year after the end of the teaching sessions for the purpose of recording the baseline, immediate post-intervention, delayed post-intervention, and long-term follow-up measurements, respectively. For participants in the control group, the meeting schedule will consist of only the four measurement sessions.

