### Data collection and management procedures

During each scheduled measurement session, the participants will be asked to take the questionnaire they were provided with in the sealed envelopes given to them at the time of enrolment that is pre-filled with the date of the appropriate measurement session. They will then be asked to hold the questionnaire sheet with the date visible to the camera and trained research support staff will check that each participant is holding the correct questionnaire. They will then walk the participants through how to fill in the questionnaire. Once they confirm that the questionnaires have been filled, they will walk the participants through how to take a photograph of the sheet and send the photo to the staff member via WhatsApp. Once the staff member receives legible photographs of the filled questionnaires from all participants, the meetings will be ended. The project staff will then save the photographs into as portable document format files on a secure computer situated in the research office of our organization and print out the same for our records. Our organization’s policy is to store both soft and hard copies of all research material—the soft copies are stored for a period of 2 years and the hard copies are stored for a period of 10 years. The research team will have unrestricted access to the final dataset.

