### Plan for handling missing data and protocol deviations

In case we are unable to recruit the required number of participants for the study from only Chennai and Dhanbad during the envisaged recruitment period, we will open the recruitment to the remaining locations that Samanjasa Foundation operates in, i.e., Hyderabad and Bhubaneshwar, India, and extend the recruitment period by another 4 weeks. Consequently, the timelines for the baseline measurements, interventions, and all post-intervention measurements will be delayed by 4 weeks. To minimize missing data, the participants will be given clear written instructions in their mother tongue and the project staff will regularly follow-up with the participants to ensure that they will not drop out of the study. Before the scheduled meetings, the participants will receive text messages and a phone call reminder from the project staff. Depending on post-hoc power analysis results, missing data will be handled either by complete case analysis or multiple imputation. Protocol deviations may result from technology failure and failure of the participants to comply with the interventions. The clear written instructions to the participants in their mother tongue and regular follow-up by project staff will help facilitate participant compliance. In case of technology failure, the project staff will video call the participants through WhatsApp, as the participants are more familiar with it than with Zoom. To prevent technology failure due to running out of data, all participants will receive an unlimited data recharge with one month validity one day before the scheduled baseline, delayed post-intervention, and long-term follow-up measurements. This can also serve as an incentive to the participants to attend the scheduled measurement sessions and help minimize missing data. In case of technology failure due to other reasons, the participants will be offered catch-up sessions before the next scheduled session.

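### The Timeline's week numbers cannot deliver the 1-day, 40-day and 1-year K10 visits; Week 56 is 15–28 days short of one year

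*Protocol article*

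**What the plan says.** The K10 is the primary outcome. The abstract places it at "one day before intervention, one day after intervention completion, 40 days post-intervention, and 1 year post-intervention". The Interventions section agrees, setting the two later visits at "40 days after the end of the teaching sessions, and 1 year after the end of the teaching sessions". The Gita course is given as "all verses) for 1 week, for 60 minutes per day", and the Kuchipudi and Both courses also run for one week. Controls attend the four measurement sessions only.

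The Timeline section turns this into study weeks: "Baseline measurements will be conducted in Week 5, interventions in Weeks 6–7, and post-intervention assessments in Weeks 8, 12, and 56". It continues, "Interim analysis shall be conducted in Weeks 13–19", and puts the final analysis in Weeks 57–61.

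The visit dates are fixed early. Each sealed envelope holds "four copies of a questionnaire with pre-filled participant ID and follow-up date, meeting schedule" (Participants), and at each session staff check on camera that the sheet is the one "pre-filled with the date of the appropriate measurement session" (Data collection and management procedures). If recruitment falls short, "the timelines for the baseline measurements, interventions, and all post-intervention measurements will be delayed by 4 weeks" (Plan for handling missing data and protocol deviations).

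**The concern.** The Interventions section ties each visit to the course, while the Timeline ties it to a study week. If the two disagree, the times of the primary outcome are stated in two incompatible ways.

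The consequence depends on which one the staff follow when they print the dates:

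- **Dates taken from the Timeline.** All three follow-up measurements can be mistimed. The immediate K10 of a Week 6 course comes more than a week after the last class, the 40-day K10 of a Week 7 course comes early, and the 1-year K10 comes early for everyone. The camera check would then confirm the wrong date.
- **Dates taken from Interventions.** The visits are right, but the final analysis is scheduled to open before any 1-year measurement exists, and some 40-day visits fall inside the interim analysis window.

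The 4-week recruitment contingency moves the schedule as a block. It adds no error, but it carries the same gaps forward.

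**Working it through.** **Convention.** Week k covers days 7(k−1)+1 to 7k. The gaps below do not depend on where counting starts.

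- Week 5 = days 29–35
- Weeks 6–7 = days 36–49
- Week 8 = days 50–56
- Week 12 = days 78–84
- Week 13 = days 85–91
- Week 56 = days 386–392
- Week 57 = days 393–399
- Week 59 = days 407–413
- Week 60 = days 414–420

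**Every 7-day course that fits in Weeks 6–7.** Start s = 36 to 43 and end e = s + 6, with visits at s − 1, e + 1, e + 40 and e + 365. Study week in brackets; bold marks agreement with the Timeline.

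| Start | End | Baseline | 1-day | 40-day | 1-year |
|---|---|---|---|---|---|
| 36 | 42 | **35 (5)** | 43 (7) | **82 (12)** | 407 (59) |
| 37 | 43 | 36 (6) | 44 (7) | **83 (12)** | 408 (59) |
| 38 | 44 | 37 (6) | 45 (7) | **84 (12)** | 409 (59) |
| 39 | 45 | 38 (6) | 46 (7) | 85 (13) | 410 (59) |
| 40 | 46 | 39 (6) | 47 (7) | 86 (13) | 411 (59) |
| 41 | 47 | 40 (6) | 48 (7) | 87 (13) | 412 (59) |
| 42 | 48 | 41 (6) | 49 (7) | 88 (13) | 413 (59) |
| 43 | 49 | 42 (6) | **50 (8)** | 89 (13) | 414 (60) |

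The Timeline fits the baseline for 1 course of 8, the 1-day visit for 1, the 40-day visit for 3 and the 1-year visit for none. No course fits more than two of the four.

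**1-year visit.**
- Week 56 falls 386 − 49 = 337 to 392 − 42 = 350 days after the course ends.
- The shortfall against 365 is 15 to 28 days.
- Counted from the Week 5 baseline instead, it is 386 − 35 = 351 to 392 − 29 = 363 days, still under a year.
- For Week 56 to be right, the course would have to end on days 21–27, before teaching starts.

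**1-day to 40-day gap.**
- Required for any participant: 40 − 1 = 39 days.
- Available between Week 8 and Week 12: 78 − 56 = 22 to 84 − 50 = 34 days.
- Equivalently, Week 8 needs a course ending on days 49–55 and Week 12 needs one ending on days 38–44. The ranges do not overlap.

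**Mistiming if the Timeline dates are used.**
- Week 6 course, immediate K10: 50 − 42 = 8 to 56 − 42 = 14 days after the last class, instead of 1.
- Week 7 course, 40-day K10: 78 − 49 = 29 to 84 − 49 = 35 days.

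**Analysis windows if the Interventions dates are used.**
- The final analysis opens on day 393; the earliest 1-year visit is day 407.
- For courses ending on days 45–49, the 40-day visit is on days 85–89, inside the interim window that opens in Week 13.

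**Other readings tried.**
- One year as 364 days: Week 56 is 14–27 days short.
- A 5-day course: 13–28 days short.
- One 14-day course filling Weeks 6–7: the baseline (day 35, Week 5) and 1-day visit (day 50, Week 8) fit, but this contradicts the one-week course, and the 40-day visit (day 89, Week 13) and 1-year visit (day 414, Week 60) still miss.

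**The case against.** The strongest reply is that the Interventions section governs. It says when the meetings are to be scheduled, the envelope carries that meeting schedule, and nothing links the pre-filled dates to the Timeline. On that reading the Timeline is a planning summary, and the true 1-year visits in Weeks 59–60 still fall within the final analysis window of Weeks 57–61. This largely stands: mistimed measurements are a risk only if the Timeline sets the dates. What remains is that the analysis window opens before any 1-year data are due.

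A second reply is that two weeks allotted to a one-week course suggest two waves. Week 5 and Week 12 would belong to the Week 6 wave, and Week 8 to the Week 7 wave. This is possible, but the list is then incomplete: it omits the Week 7 wave's baseline (Week 6), the Week 6 wave's 1-day visit (Week 7) and the Week 7 wave's 40-day visit (Week 13). It does nothing for Week 56.

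A third reply is that Fig 3 holds the detailed timeline, and I could not see it. It may list waves, but it cannot make the stated Week 56 one year after teaching.

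Finally, the counts out of eight depend on sharp week boundaries. They illustrate the conflict; the 15–28 day shortfall and the 39-day gap carry the point.

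**Conclusion.** The concern holds, as a minor inconsistency. Week 56 is 15–28 days (about 4–8% of a year) short of one year after any 7-day course in Weeks 6–7, and Weeks 8 and 12 cannot be the same participant's 1-day and 40-day visits. The 1-year time is the only one that is impossible for every course on its own; the others fail as a set.

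This rests on seven-day weeks numbered consecutively, a 7-day course held wholly within Weeks 6–7, and 365 days to the year. The variants tried do not rescue Week 56. The sample size and analysis model are unaffected. Controls have the same four sessions, so a timing shift shared by all arms does not by itself bias the group comparison.

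**What to change.** Let the Interventions section govern and correct the Timeline sentence. With teaching kept in Weeks 6–7, it should read: baseline Weeks 5–6, immediate K10 Weeks 7–8, 40-day K10 Weeks 12–13 and 1-year K10 Weeks 59–60. If all teaching is in Week 6, the four K10 days are 35, 43, 82 and 407.

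Set the pre-filled questionnaire and meeting dates from each course's own teaching days, with controls matched to the same dates. If teaching is staggered, include all four arms in each wave.

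Start the interim analysis after the last 40-day visit (day 89 at the latest) and the final analysis after the last 1-year visit (day 414 at the latest).

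**Cost.** One corrected sentence and matching dates; visits and participants do not change. The final analysis can start on day 408 to 415 instead of day 393, which is 15–22 days later, or 3–4 weeks if moved to the next whole week (Week 60 or 61). The interim analysis starts at most one week later.

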## Blinding

The study will involve three separate teams—trained teachers, project staff, and the research team. Trained teachers will be responsible for administering the interventions; the teachers will be blinded to the K10 results. Project staff will be responsible for ensuring participant compliance, collecting the filled K10 questionnaires as photos via WhatsApp, and printing the photos and storing them until data analysis; project staff will be blinded to data analysis. The research team will be responsible for study design, participant recruitment, obtaining written informed consent, data analysis and reporting; the research team will be blinded to participant group allocation.

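### The Timeline starts dissemination events once the 40-day interim analysis is published, before the 1-year K10 and against the dissemination plan, and its weeks do not reproduce the 40-day and 1-year visits

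*Protocol article*

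**What the plan says.** **Timing of results.** The Timeline section of the protocol article states "Interim analysis shall be conducted in Weeks 13–19, and results will be published as the Stage II of this registered report" and then "Final analysis will be conducted in Weeks 57–61, and results shall be published as a brief report". Conferences, meetings, workshops and other community events to share results are to run indefinitely, "starting from the date of publication of the interim analysis as a registered report".

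The section on dissemination of results begins differently: "Upon completion of the trial, a comprehensive plan for dissemination and publication of the results will be implemented". The Abstract also places sharing of findings after the study is complete. The dissemination section names the audience. It includes people experiencing homelessness, reached through community meetings, peer educators and WhatsApp.

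**Timing of visits.** The Interventions section defines the post-intervention measurements as "one day after the end of the teaching sessions, 40 days after the end of the teaching sessions, and 1 year after the end". Teaching is given daily for one week (for the Gita group, "all verses) for 1 week, for 60 minutes per day"). The Timeline places the same events in calendar weeks: "Baseline measurements will be conducted in Week 5, interventions in Weeks 6–7, and post-intervention assessments in Weeks 8, 12, and 56".

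**Analysis.** The primary outcome is the K10, measured at four times, with none named as primary. Data analysis sets one two-tailed 0.05 level. Bonferroni is applied to pairwise post-hoc group comparisons. The article's SAP section does not mention the interim analysis.

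**The concern.** The article gives two incompatible starting points for dissemination, and the earlier one falls before the last primary-outcome measurement. Three features of the design make that matter:

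- The K10 is self-completed, and the article's own limitations section accepts that sole reliance on self-report may introduce response bias.
- Participants know whether they were taught something or received nothing. The Blinding section covers teachers, project staff and the research team only.
- Project staff collect the K10. Under the risk mitigation strategy they are drawn from volunteers who engage regularly with these clients, so they are likely to hear any results shared in the community.

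A participant who learns at such an event which arm did better may answer the 1-year K10 with a changed expectation, and a control participant may take up the favoured practice. Either would bias the 1-year comparison, and analysis could not readily undo it. The planned contamination adjustment measures exposure to details of other groups' interventions, not exposure to trial results.

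The visit weeks matter because they decide when each analysis can start. If they are wrong, an analysis may open before its last visit, or a visit may be held too early.

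**Working it through.** **1. Dissemination passages side by side**

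| Section | Start of dissemination |
|---|---|
| Abstract | after study completion |
| Plan for dissemination of results | on completion of the trial |
| Timeline | from publication of the interim analysis |

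The third row cannot stand with the first two, because the 1-year K10 is still to come when the interim report appears.

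**2. Lead time before the 1-year K10**

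No publication date is given. Assume publication at the end of the interim analysis window, Week 19.

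- To the stated 1-year assessment: 56 − 19 = 37 weeks.
- To a true 1-year date (Week 59 or 60, step 3): 59 − 19 = 40 or 60 − 19 = 41 weeks.
- Any delay in publication shortens both.

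**3. Calendar**

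Day d falls in week floor((d − 1)/7) + 1. A one-week course held within Weeks 6–7 ends between day 42 (last day of Week 6) and day 49 (last day of Week 7).

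| Teaching ends | +1 day | +40 days | +365 days |
|---|---|---|---|
| day 42 | day 43, Week 7 | day 82, Week 12 | day 407, Week 59 |
| day 44 | day 45, Week 7 | day 84, Week 12 | day 409, Week 59 |
| day 45 | day 46, Week 7 | day 85, Week 13 | day 410, Week 59 |
| day 49 | day 50, Week 8 | day 89, Week 13 | day 414, Week 60 |
| Stated in Timeline | Week 8 | Week 12 | Week 56 |

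No row reproduces the stated set.

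- *Week 56* is days 386 to 392. That is 386 − 49 = 337 days after teaching at the least and 392 − 42 = 350 at the most, so 15 to 28 days short of 365.
- *Weeks 8 and 12 together.* From the first day of Week 8 to the last day of Week 12 is 4 × 7 + 6 = 34 days. The 1-day and 40-day visits are 40 − 1 = 39 days apart. Week 12 fits alone if teaching ends by day 44, but the 1-day visit is then in Week 7.
- *Weeks 8 and 56 together.* The longest span is 48 × 7 + 6 = 342 days; 364 are needed.
- *Analysis windows.* Week 57 opens on day 393, which is 14 to 21 days before the 1-year date (days 407 to 414). If the 1-day visit is in Week 8, the 40-day visit is day 89 at the earliest, and the interim window has already opened on day 85 (first day of Week 13).

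**4. Two reports on one primary outcome (illustrative)**

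Take one contrast tested two-sided at 0.05 in each report. The chance of at least one false rejection is 1 − P(|Z₁| < 1.96, |Z₂| < 1.96), with (Z₁, Z₂) bivariate normal. The sample size section assumes ρ = 0.5 between repeated measures, and the primary analysis assumes an exchangeable structure.

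- *40-day and 1-year contrasts each counted.* Taking 0.5 as the correlation between the two tests gives 9.1%.
- *Average post-intervention effect.* In units of the K10 variance, the variance of the mean of two visits is (1 + 0.5)/2 = 0.75, that of three visits is (1 + 2 × 0.5)/3 = 0.667, and their covariance is (2 + 4 × 0.5)/6 = 0.667. The correlation is 0.667/√(0.75 × 0.667) = 0.943, which gives 6.6%. Taking change from baseline leaves these values unchanged at ρ = 0.5.

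At 0.05/3 per contrast (three arms against control under Bonferroni), the same calculation gives 2.3% (correlation 0.943) and 3.1% (correlation 0.5), against a nominal 1.7%.

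**The case against.** The strongest reply is that this is a conflict of wording. The Timeline speaks of conferences, meetings, workshops and community events in general. The channels aimed directly at homeless people appear only in the dissemination section, under trial completion. A reader might infer that participants will be told which arm worked before their last K10. The documents do not establish that; they show only that the Timeline permits it and that other sections point the other way. This part of the objection stands, and the point is worded accordingly.

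Other fair replies:

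- *The interim analysis is not a group-sequential look.* No stopping rule is attached, and it reports the complete data to 40 days. A reader might infer a missing stopping boundary or a trial-wide error of 9.1%. Neither follows. The 6.6% to 9.1% is per contrast, before the pairwise Bonferroni. What remains is two published analyses of one primary outcome with no primary time point.
- *Analyst blinding.* A reader might infer that the interim report breaks the statement that "the research team will be blinded to participant group allocation". Arm-level results need not reveal individual allocation, and the article does not describe how groups are coded for analysis, so this is not claimed.
- *Contamination controls exist.* Weekly messages, spot checks, covariate adjustment and exclusion analyses are planned. They address exposure to intervention details, so they help only in part.
- *The weeks are a summary.* The visits are defined in days, questionnaires are pre-filled with dates, and the Timeline figure is not shown. A true 1-year visit still falls inside the Weeks 57–61 window. This lowers the practical risk, but the stated weeks still cannot all hold.
- *Staged reporting is legitimate.* Agreed. Publishing the 40-day results in a journal is not the problem; feeding comparative results back to participants and their data collectors is.

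**Conclusion.** Two findings hold on the text alone. First, the Timeline contradicts the Abstract and the dissemination plan on when results are shared, and following the Timeline could expose participants and project staff to comparative results before a self-reported primary-outcome measurement. The size of any resulting bias cannot be computed from the documents. The lead time is up to about 37 weeks on the stated schedule, or 40 to 41 weeks to a true 1-year date, assuming publication in Week 19.

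Second, the stated weeks do not reproduce the defined visits. The Week 56 mismatch (15 to 28 days short) holds wherever the one-week course falls within Weeks 6–7. The Week 12 mismatch holds only in combination with Week 8.

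The alpha point is secondary. Its figures rest on ρ = 0.5 and on testing a single contrast at the full 5% in each report.

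**What to change.** 1. Amend the Timeline to agree with the Abstract and the dissemination plan. State explicitly that no comparative result goes to participants, case workers or project staff, by community event or digital platform, until the last 1-year K10 is collected. The dissemination section implies this timing but contains no such restriction, so it has to be written. Journal publication of the Stage II report may proceed.
2. Reconcile Weeks 8, 12 and 56 with the 1-day, 40-day and 1-year definitions, and open each analysis only after its last visit.
3. Name one confirmatory time point and label the other report secondary, or split alpha between the two reports (for example 0.025 each).

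The cost is later community feedback, by roughly the lead time above; the rest is wording. If alpha is split rather than a time point named, each report is tested at a stricter level.
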